### Statistical methods

Statistical analysis will be conducted using STATA version 18 (StataCorp, College Station, TX). All statistical tests will use 5% significance levels and 95% confidence intervals. Descriptive statistics (mean, standard deviation, counts, and percentage) shall be used to summarise both effectiveness and implementation outcomes at baseline and 3-, 6-, and 12-month follow-up time points by allocation groups. Assumptions of all parametric tests (such as normal distribution) where applicable and the presence of missing data at random will be evaluated; if not met, appropriate transformation or multiple imputation methods will be considered.

A mixed effects linear regression model will be used with a PHQ-9 score at 6 months as the outcome for the primary effectiveness endpoint. We will use the PHQ-9 baseline score and other important baseline variables as fixed effects and clinics as random effects to account for the clustered nature of the data. The same models (or logistic mixed effects model in case of binary outcome) will be used for other individual-level secondary variables, where applicable. All the analyses will be based on the intention-to-treat principle.

On the other hand, generalised linear model with a log link function and binomial distribution will be used for ‘reach’ (participants who received treatment divided by those eligible for treatment) as an aggregated implementation outcome to compare allocation groups while using some important clinic-level factors as covariates such as availability of EMR (present vs absent) and average attendance per month (small < 1000, medium 1001–3000, large > 3000). All other clinic-level data will be analysed using the same model, where comparisons across groups are applicable. Some clinic-level data captured only in the intervention group, such as adoption, will be summarised using descriptive statistics.

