#### Secondary outcomes—effectiveness

The prevalence of case-level depression by allocation groups will be measured using PHQ-9 scores; a score < 10 indicates recovery, while ≥ 10 indicates case-level depression [37, 49, 50].The severity of anxiety will be measured by the mean change in GAD-7 scores from baseline to follow-up time points, across allocation groups. We will also assess the caseness of anxiety by allocation groups, using a GAD-7 score of ≥ 6 to indicate the clinical case-level of anxiety [38, 42].The mean change in Health Related Quality of Life (HRQoL) from baseline to follow-up time points, by allocation groups, will be measured using the EuroQol Five-Dimensional Scale, five levels (EQ-5D-5L) instrument [43].The severity of functional impairment will be measured by the mean change from baseline to follow-up time points by allocation groups using the World Health Organization Disability Assessment Schedule (WHODAS 2.0) [44].Anthropometric measures include BMI, BP, and waist circumference [51].Healthcare resource use will be assessed using a modified Client Service Receipt Inventory (CSRI). We will collect data covering several aspects including (i) outpatient and inpatient visits/admissions, (ii) medical tests, (iii) medicines, and (iv) details of specialities consulted. Costs will include total healthcare and out-of-pocket costs, including intervention costs [45].Economic outcomes such as household expenditures and assets, productivity loss, and catastrophic healthcare costs will also be collected. This will be collected using the International Wealth Index (IWI) and some items will be developed purposefully to capture this detail [41].Serious adverse events will be recorded and reported immediately, while adverse events will be recorded in follow-up.

Depression, anxiety, quality of life, anthropometric measures, and adverse events will be assessed at 3, 6, and 12 months. All other outcomes will be assessed at 6- and 12-month follow-up.

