### Sample size

We calculated our sample size based on a recent meta-analysis of CC [13] with a pooled standardised effect size of − 0.51 (95% confidence interval (CI) − 0.80 to − 0.23) for depression outcomes measured up to 6 months. Using an estimate closer to the lower bound, i.e. − 0.35, which is approximately equivalent to 1.4 points on PHQ-9 (assuming SD = 4), we will require 720 participants from 24 clinics (~ 30 participants per clinic) and need to screen approximately 12,000 (assuming 10% depression prevalence, 60% consent rate, 20% attrition, − 0.35 standardised effect, 90% power, 5% alpha, 0.03 intraclass correlation coefficient and design effect of 1.69) to evaluate the clinical effectiveness of CC for depression.

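### The trigger for multiple imputation is inverted: it is tied to missing-at-random failing, which cannot be checked and is the assumption that standard imputation needs

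*Protocol article*

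**What the plan says.** The missing-data rule is one sentence in the Statistical methods section of the protocol article. It opens with "Assumptions of all parametric tests (such as normal distribution) where applicable" and continues: "the presence of missing data at random will be evaluated; if not met, appropriate transformation or multiple imputation methods will be considered". So it names two checks (distributional assumptions and MAR) and two remedies (transformation and multiple imputation).

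The primary analysis is given in the next paragraph: "A mixed effects linear regression model will be used with a PHQ-9 score at 6 months as the outcome for the primary effectiveness endpoint". Its terms are these: "We will use the PHQ-9 baseline score and other important baseline variables as fixed effects and clinics as random effects". The same paragraph adds: "All the analyses will be based on the intention-to-treat principle".

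The Secondary outcomes—effectiveness section sets the visits: "Depression, anxiety, quality of life, anthropometric measures, and adverse events will be assessed at 3, 6, and 12 months". Table 1 also lists PHQ-9 severity at 3 and 12 months as a secondary outcome. The 3-month PHQ-9 will therefore exist for many participants who are missing at 6 months.

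The Sample size section assumes "20% attrition, − 0.35 standardised effect, 90% power, 5% alpha, 0.03 intraclass correlation coefficient and design effect of 1.69". No other part of the article gives a missing-data method or a different trigger for imputation.

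**The concern.** Transformation answers non-normality, so multiple imputation is left as the answer to MAR not being met. That pairing has two faults.

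- The check cannot be done. Observed data can show departures from missing completely at random (MCAR). They cannot separate MAR from missing not at random (MNAR), because the difference lies in the values that were not seen.
- The remedy does not fit the diagnosis. Standard multiple imputation relies on MAR. The rule brings it in when MAR is thought to fail and does not call for it when MAR is thought to hold, which is where it works.

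At stake is the primary effectiveness estimate. A participant without a 6-month PHQ-9 contributes nothing to the stated primary model, even with a 3-month score on file. Participants know which care they receive and the arms receive different care, so dropout could plausibly follow early response, and differently by arm.

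**Working it through.** **Inputs.** From the Sample size section: standardised effect 0.35 (1.4 PHQ-9 points at SD 4), 90% power, 5% alpha (taken as two-sided), intraclass correlation 0.03, 24 clinics of about 30, 20% attrition. From Statistical methods: the model terms and the missing-data rule quoted above.

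**1. The plan's own figure.**
- Per arm before clustering: 2 × (1.96 + 1.2816)² / 0.35² = 171.5, so 172.
- Analysed per clinic: 30 × 0.8 = 24. Design effect: 1 + (24 − 1) × 0.03 = 1.69, as stated.
- Total analysed: 2 × 172 × 1.69 = 581. Total recruited: 581 / 0.8 = about 727, against 720 stated. Power at 720 is 89.8%.

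The sample size reproduces closely and is not in dispute. It implies 720 × 0.2 = 144 missing 6-month scores.

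**2. The two branches of the rule.**
- MAR judged to hold: imputation is not triggered, and the analysis is the available-case mixed model. It is valid if missingness depends only on arm and the included covariates. If missingness also depends on the 3-month PHQ-9, the data can still be MAR given that score, but this model does not condition on it.
- MAR judged to fail: imputation is considered, although its standard form assumes what has just been rejected.

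**3. Illustration by simulation.** There were 1,500 trials per mechanism, with 24 clinics of 30, SD 4, intraclass correlation 0.03, true effect −1.40 and about 20% missing. In the two informative cases, dropout rose with worse scores in the intervention arm only. The dropout mechanisms, their strength and the correlations between visits are assumptions, not figures from the article. Both analyses used baseline-adjusted linear regression without a clinic effect, so only the average estimates are read here. Imputation was by arm, from the baseline and 3-month scores.

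| Mechanism | Available cases | Imputation |
|---|---|---|
| MCAR | −1.41 | −1.41 |
| MAR given the 3-month score | −1.76 | −1.40 |
| MNAR (depends on the 6-month score) | −2.01 | −1.80 |

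The Monte Carlo standard error is about 0.01. In the MAR row the available-case error is 1.76 − 1.40 = 0.36 points, or 0.36 / 1.4 = 26% of the target effect, and it exaggerates the benefit. Imputation removes it. In the MNAR row imputation is still off by 1.80 − 1.40 = 0.40 points.

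**4. What a delta calculation shows.** If missing scores in one arm (20% missing) are 1, 2 or 3 points worse than modelled, the arm difference shifts by 0.2 × 1, 2 or 3 = 0.2, 0.4 or 0.6 points, which is 14%, 29% or 43% of 1.4. This is sensitivity to MNAR under assumed deltas. It would apply equally to any MAR-based analysis, including the one proposed below, so it does not measure the harm of this rule.

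**The case against.** The sentence is tentative and may simply be loose. It says that methods will be considered, and it does not say that imputation is used only when MAR fails; that restriction is inferred from the condition. If the authors meant MCAR, the check is feasible and turning to imputation on its failure would be conventional. This softens the point but does not remove it, because the text says missing at random and nothing elsewhere corrects it.

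A reader might infer that neither branch protects the primary estimate. The article does not support that. The baseline-adjusted mixed model is already valid if missingness depends only on arm and its covariates. In the MNAR illustration, imputation was also closer to the truth than available cases (−1.80 against −2.01).

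A reader might also take the 14%, 29% and 43% shifts as the size of the damage. They are not, for the reason given in step 4.

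Finally, a single-timepoint adjusted mixed model is a standard primary analysis, and the imputation model and sensitivity analyses are commonly left to a statistical analysis plan, which is not shown. The absence of an MNAR analysis from the article is therefore not counted as a fault. What stands is the decision rule that the article does state, and which an analysis plan following it would inherit.

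**Conclusion.** The point holds as a should-fix. The stated trigger is inverted as written, and the check that it depends on cannot be made. Its practical consequence is that an available-case model of the 6-month score becomes the default, leaving out a 3-month score that could correct for dropout related to early response.

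The size is conditional. If missingness depends only on arm and the model's covariates, there is no bias to correct. If dropout follows the 3-month PHQ-9 differently by arm, the bias can matter: 0.36 points, about a quarter of the 1.4-point target, in the one assumed case worked above. If the dependence were the same in both arms, the errors would largely cancel in the difference. The article gives no figures to choose among these cases, and the 20% attrition is a planning allowance.

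**What to change.** Delete the condition that ties imputation to MAR not being met. If a check against MCAR was meant, say so and treat it as descriptive. State MAR as the working assumption of the primary analysis.

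Bring the 3-month PHQ-9 in by default, in one of two ways:
- multiple imputation carried out separately by arm, respecting clinic clustering, with the 3-month score in the imputation model; or
- a repeated-measures mixed model of the follow-up PHQ-9 scores with clinic and participant effects, and the 6-month contrast as primary.

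Examine departures from MAR in a sensitivity analysis, for example delta-adjusted by arm. This detail can sit in the statistical analysis plan.

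The cost is a change of wording and modest extra programming, with no new data and no change to the 720. The Trial status section reports 598 of 720 recruited by 15 January 2026 and recruitment running to 31 March 2026, so the last 6-month assessments fall around the end of September 2026. The change can be made before outcome data are examined by arm.

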**Methods:**

A hybrid type-II effectiveness-implementation cluster randomised controlled trial with embedded process and economic evaluations will be conducted. Twenty-four primary care clinics located in socioeconomically disadvantaged areas of Karachi will be randomly allocated (1:1) using minimisation to either (i) a contextually adapted collaborative care model for depression supported by co-designed implementation strategies or (ii) optimised usual care (routine practice with additional depression screening and provision of information leaflets about depression for those screening positive). Participants aged 18 years or above, scoring ≥ 10 on the 9-item Patient Health Questionnaire (PHQ-9) and not under any active treatment for depression, will be recruited. The Reach, Effectiveness, Adoption, Implementation and Maintenance framework will guide our outcome evaluation. The primary clinical outcome will be depression severity, assessed using the PHQ-9 at 6 months after participant recruitment. The primary implementation outcome will be ‘reach’ (proportion calculated as the number of people who participated in depression treatment divided by those eligible for such treatment) using routine, clinic-level aggregated data at 6 months. The process evaluation will explore factors such as fidelity, acceptability and sustainability of collaborative care using a mixed-methods approach guided by the Consolidated Framework for Implementation Research. A within-trial economic evaluation will explore the cost-effectiveness of both collaborative care and implementation activities. Individual-level effectiveness outcomes will be analysed using mixed-effect linear regression; and clinic-level implementation outcomes using generalised linear regression. Trial data analysis will be based on an intention to treat principle.

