#### Primary outcome—implementation

Our primary outcome is the reach of depression treatment, measured by calculating the proportion of eligible individuals (score on PHQ-9 ≥ 10) who participate in treatment for depression (having ≥ two contacts with healthcare staff) 6 months after the CC rollout in the clinics, i.e. when clinic staff start practising CC in their clinics, referred to as the ‘start date’.

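### The binomial model stated for reach, the primary implementation outcome, makes no allowance for variation between clinics, although clinics are the randomised unit

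*Protocol article*

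**What the plan says.** All references are to the protocol article. Clinics are the unit of randomisation (Randomisation): 24 clinics, allocated 1:1. The abstract names reach as the primary outcome for implementation, and Table 1 lists it beside PHQ-9 under primary outcomes. It is the share of people with PHQ-9 of 10 or more "who participate in treatment for depression (having ≥ two contacts with healthcare staff) 6 months after the CC rollout in the clinics".

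Statistical methods treats the two primary outcomes differently. For PHQ-9 at 6 months the model has "clinics as random effects to account for the clustered nature of the data". For reach, by contrast, a "generalised linear model with a log link function and binomial distribution will be used for" the outcome, taken "as an aggregated implementation outcome to compare allocation groups while using some important clinic-level factors as covariates". Availability of electronic medical records (EMR) and average attendance are given as examples of those covariates. The model then carries over: "All other clinic-level data will be analysed using the same model, where comparisons across groups are applicable". The abstract makes the same split, with mixed-effect regression for individual outcomes and generalised linear regression for clinic-level ones.

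The only correlation figure in the article is in Sample size, for PHQ-9: "0.03 intraclass correlation coefficient and design effect of 1.69".

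**The concern.** Adding patients up to clinic totals does not remove clustering. A binomial likelihood on 24 totals is the same, up to a constant, as one that treats every eligible patient as an independent observation. Its standard error shrinks with the number of patients rather than the number of clinics. Two clinic-level covariates cannot be expected to absorb all remaining variation between clinics, which differ in staffing and deliver treatment through their own counsellors.

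At stake is one of the trial's two primary comparisons. Ordinary clinic-to-clinic variation could be reported as an effect of the implementation package, with an interval that is too narrow. The same applies to every other clinic-level outcome compared between arms. Reach of screening has all attenders as its denominator, so its clinic denominators are larger still.

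**Working it through.** **1. The plan's own figure.** Inputs from Sample size: effect 0.35 SD, 90% power, 5% alpha (two-sided assumed), ICC 0.03, 20% attrition, 24 clinics of about 30.
- Per arm: 2 x (1.960 + 1.282)^2 / 0.35^2 = 172 after rounding up, so 344 in total.
- Design effect: 30 x 0.8 = 24 analysed per clinic, and 1 + (24 - 1) x 0.03 = 1.69, as stated.
- 344 x 1.69 = 581.4, and 581.4 / 0.8 = 727, against 720 stated (within 3%).
- Screening: 720 / (0.10 x 0.60) = 12,000, as stated.

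The sample size therefore allows for clustering, but for PHQ-9 only.

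**2. Inputs for reach.** The article gives neither an ICC nor an expected denominator.
- Eligible per clinic, m: the recruitment screening figures give 12,000 x 0.10 / 24 = 50. Reach uses routine data on the whole clinic population, so 50 may be low. I take 300 as a second value (assumption).
- ICC: range 0.005 to 0.10 (assumption). The value 0.03 is borrowed from PHQ-9.

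**3. Formula.** Design effect DE = 1 + (m - 1) x ICC. The unadjusted standard error is too small by a factor of sqrt(DE). The true size of a nominal 5% test is 2 x (1 - Phi(1.96 / sqrt(DE))).

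| ICC | DE, m = 50 | Type I error | DE, m = 300 | Type I error |
|---|---|---|---|---|
| 0.005 | 1.25 | 7.9% | 2.50 | 21.5% |
| 0.01 | 1.49 | 10.8% | 3.99 | 32.6% |
| 0.03 | 2.47 | 21.2% | 9.97 | 53.5% |
| 0.05 | 3.45 | 29.1% | 15.95 | 62.4% |
| 0.10 | 5.90 | 42.0% | 30.90 | 72.4% |

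At m = 50 and ICC 0.03, sqrt(2.47) = 1.57, and a nominal 95% interval covers about 79%.

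**4. Simulation check.** 1,500 null trials per setting, 12 v 12 clinics of equal size, beta-binomial counts, true reach 0.5, log-link binomial model on clinic totals with arm only.
- m = 50: 4.6% at ICC 0, then 11.4% (0.01), 20.9% (0.03), 30.7% (0.05) and 42.7% (0.10).
- m = 300: 5.9% at ICC 0, then 32.1%, 51.1%, 61.1% and 74.8% at the same ICCs.
- m = 50, ICC 0.03, clinic sizes with coefficient of variation 0.6: 25.7%. With equal sizes and reach 0.3: 21.1%.

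**5. Which correction holds its level.** With equal clinic sizes, the same model with a Pearson scale and t on 22 degrees of freedom gave 3.3-5.3%, and a t-test on clinic proportions gave 4.3-5.7%. With coefficient of variation 0.6 they gave 7.0% and 5.5%.

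The attendance bands in Randomisation (below 1,000, up to 3,000, and above) suggest a wider spread. A further simulation used sizes in ratio 0.5:2:5 (assumption), reach 0.4 and 4,000 runs. The Pearson scale with t gave 8.8% at m = 50, ICC 0.03 (9.4% with EMR and size covariates), 11.3% at m = 300, ICC 0.03, and 11.7% at m = 300, ICC 0.10. The unweighted t-test on clinic proportions stayed at 4.6-5.4%. The reason is that extra-binomial variance grows with clinic size, which one constant scale cannot represent.

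**The case against.** The best defence is that a condensed article names the mean model, family and link but not the variance estimator. The stated family and link are compatible with robust or scaled errors, and such detail often sits in an analysis plan, which is not shown. So a reader should not infer that the sponsor has decided on unadjusted errors; the text does not show that. The defence is weakened because the same section does address clustering for PHQ-9 and then sets reach apart with a different, fully named model. Its general check of assumptions offers only transformation or multiple imputation, and neither repairs extra-binomial variance.

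Other objections stand and limit the point:
- A reader might conclude that the error bars are far too narrow whatever the data. That is conditional. At 50 per clinic and ICC 0.005-0.01 the error is 8-11%. If the 24 proportions were entered with denominator 1, the test would be very conservative (no rejections in simulation), which is also invalid but in the other direction. Clinic denominators are the natural reading of a ratio with a binomial distribution.
- Reach could be called co-primary. The article says only that it is the primary implementation outcome.
- Failure of the log link to converge is possible when reach is near 1, but no expected reach is given.
- The implementation cost-effectiveness analysis is presented as incremental ratios. These rest on point estimates, which a wrong standard error does not shift.
- The extension covers only outcomes compared between arms. The article gives adoption as an example of data to be summarised descriptively.

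**Conclusion.** The model for reach is wrong as written. Followed literally, with clinic denominators, it gives standard errors that are too small for a primary outcome of a cluster-randomised trial. The direction is clear on that reading, but the amount is not, because the ICC for reach and its denominators are assumptions here. At 50 eligible per clinic the true type I error runs from about 8% (ICC 0.005) through 21% (0.03) to 42% (0.10). At 300 per clinic it runs from about 21% to 72%, and unequal clinic sizes add to it. The documents do not support a single figure, nor the claim that the published result will be false: a large true difference could survive correction, though its interval would still be wrong.

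**What to change.** Make the primary analysis of reach a clinic-level one. Regress the 24 clinic proportions (or log proportions, if a ratio is wanted) on arm and the three minimisation factors, with t-based inference on 24 minus p degrees of freedom. With an intercept, arm, attendance in three bands, EMR and prior counsellor, p = 6, which leaves 18. An acceptable alternative is a binomial model with a clinic random intercept, or a beta-binomial model, with a small-sample correction for 24 clusters. The simulations above covered the unadjusted clinic-level t-test, not these adjusted or random-effect forms.

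Do not rely on a constant Pearson scale as the main correction. Apply the same rule to the other clinic-level outcomes compared between arms, and fix it before any comparison of arms, so that the variance method is not chosen with results in view.

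The cost is one paragraph of wording and wider intervals, with no new data. An unweighted clinic-level analysis also counts each clinic equally rather than by its eligible patients, and the text should say so.
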